#### Control Group

In addition to usual care, the Control group will be provided with e-messages following the same delivery schedule (Table 1). The e-messages will include brief articles that are randomly selected from the Healthy Living section of the Heart and Stroke Foundation of Canada e-platform. Each e-support article will provide information tailored for a CHF population, such as appointments with physicians and advice about heart healthy guidelines for exercise, diet, smoke-free living, symptom monitoring, and medications. This intervention will be distinct from the e-Counseling group in two ways: (1) information will not be tailored to each subject’s stage of readiness for change, and (2) e-messages will not include e-tools and e-Counseling procedures to increase “readiness” and efficacy to adhere to targeted self-care behaviors.

### Randomization and Blinding

Protection against bias will be accomplished by double blinding. Randomization will be done through a particular website which uses randomly permuted blocks to assign subjects to the e-Counseling group or to the Control group. This process will be conducted in blocks to ensure that group assignment is balanced across our recruitment sites (Toronto, Montreal, and Vancouver) for the overall trial. The individual who will be responsible for randomization at the Behavioral Cardiology Research Unit, UHN has no direct involvement in this trial. In addition, the randomization code will be hidden from trial subjects, as well as all those who will conduct assessments, data processing, and analysis. Thus, the CHF-CePPORT research team members and the trial subjects from the three sites will not be aware of the group assignment of the subjects.

### Outcome Measures

#### Collection Materials in English and French

Data collection materials will be available in both English and French. All materials were developed in English. We will indicate if a published French version of a questionnaire is to be used. If none is available, our Montreal team will translate the English questionnaire into French using a standard back-translation protocol [74].

#### Primary Outcome

The primary outcome is quality of life improvement of subjects at the 12-month assessment, as measured by the number of subjects who demonstrate a clinically meaningful increase of ≥5 points [38] on the summary score of the KCCQ [39]. It is a 23-item questionnaire that assesses the patient’s perception of CHF in terms of physical limitations, symptoms (frequency, severity, and recent change over time), self-efficacy, social interference, and quality of life over the past 2 weeks. The summary score ranges from 0-100, with the lower score reflecting poorer quality of life. Internal consistency is high for all domains (Cronbach alphas=.78-.95), except the 2-item self-efficacy scale (Cronbach alpha=.62). We will employ a validated French-Canadian version [39] of KCCQ in this trial.

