#### Secondary Outcomes

The quality of life at the 4-month interval will be assessed by determining the number of subjects who demonstrate a ≥5-point improvement of the KCCQ total score [38,39].

The subjects’ increase in adherence to the recommended intake of vegetables, fruit, dairy, and dietary fat will be evaluated at the 4- and 12-month assessments using the Canadian version [40] of the DHQ II [75], which is also available in French.

The physical activity level of the subjects will be measured in two ways: (1) mean step count, and (2) self-report questionnaire. We will ask subjects to document their daily step count for 7 days prior to their assessments at baseline, 4-, and 12 months. The step count will be measured using an accelerometer (LifeSource/A&D XL-18CN Activity Monitor) that we will provide to each subject. We will calculate the mean 4-day step count using data from the three weekdays and one weekend day that have the highest step count out of the 7-day record [76,77]. Adherence to physical activity over the past week will be measured by the PASE [78], which has been validated in persons with CHF [79]. We will use a French version that was translated by its publisher.

We will confirm the smoking status of those who self-report as a current smoker at the baseline, 4-, and 12-month assessments using salivary cotinine. The current smokers will be defined by having salivary cotinine level ≥10 ng/ml. These subjects will also be screened for the use of nicotine replacement therapy, which can confound their salivary cotinine result. Smoking history will be evaluated using questions from the Survey on Living with Chronic Disease in Canada [80] (ie, “Have you smoked at least 100 cigarettes in your life?”). The French version [80] of the smoking history questions will be also used in this trial.

We will estimate each subject’s medication adherence using MPR [81]. It calculates the cumulative medication supply for *x* days, divided by the total days to the next reﬁll or end of the observation period. MPR has been validated in a previous trial [20]. We will measure MPR with pharmacy refill data for a 4-month period that precedes each of the three assessments.

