#### Statistical Analysis

This trial will use a 2 parallel-group design with 3 repeated assessments at baseline, 4-, and 12-months. A generalized mixed model (GMM) will evaluate the primary outcome, which is a binary code of whether the 12-month KCCQ [39] increases ≥5 points [38]. Predictors will include baseline KCCQ, age, sex, body mass index, and Group (e-Counseling vs Control). The primary outcome will be coded as a “failure” in the event of CHF hospitalization or mortality, but not for “elective” medical procedures (eg, cardiac resynchronization therapy). GMM with repeated measures will assess binary secondary outcomes across 4- and 12-month intervals (eg, KCCQ and smoking status). This analysis is optimal as it adjusts for serial correlations across repeated measures and between individual subjects in each group. Predictors will include baseline KCCQ, age, sex, body mass index, time (4- vs 12- month assessment interval), and Group (e-Counseling vs Control). Significant interactions or main effects will be followed by Bonferroni post hoc tests for significance, *P*<.05, 2-sided. Data missing at random will be handled by multiple imputations. For continuous secondary outcomes, linear mixed models (LMM) [94] for repeated measures with a random intercept will assess whether within-subject improvement across 4- and 12-month intervals is independently associated with our e-Counseling protocol. This analysis adjusts for serial correlations across repeated measures and between subjects in each Group. Predictors will include the baseline dependent variable, age, sex, body mass index, time (4- vs 12-month assessment interval), and Group (e-Counseling vs Control). LMM with a random intercept will also evaluate whether e-Counseling vs Control demonstrates improvement at the 12-month interval in VO_2_ peak, NT-proBNP, hsCRP, and the SHFM.

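### KCCQ quality of life is analysed only as a gain of at least 5 points at both visits, so no described analysis gives a mean difference with a confidence interval on the trial's central scale

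*Protocol article*

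**What the plan says.** The protocol article describes the KCCQ under Primary Outcome: "The summary score ranges from 0-100, with the lower score reflecting poorer quality of life". Data Collection sets assessments at baseline, 4 and 12 months.

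Wherever the KCCQ is an outcome, it is dichotomised:

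- **12 months, primary.** Primary Outcome defines it "as measured by the number of subjects who demonstrate a clinically meaningful increase of ≥5 points", in line with Primary Hypothesis. Statistical Analysis describes the variable as one "which is a binary code of whether the 12-month KCCQ" rises by at least 5 points.
- **4 months, secondary.** Secondary Outcomes states: "The quality of life at the 4-month interval will be assessed by determining the number of subjects who demonstrate a ≥5-point improvement of the KCCQ". Secondary Hypotheses uses the same threshold.
- **Both visits, repeated measures.** Statistical Analysis says: "GMM with repeated measures will assess binary secondary outcomes across 4- and 12-month intervals (eg, KCCQ and smoking status".

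The score itself appears in the models only as a baseline covariate: "Predictors will include baseline KCCQ, age, sex, body mass index, and Group (e-Counseling vs Control". Linear mixed models (LMM) with a random intercept are kept for continuous secondary outcomes, and no section names the KCCQ as one of these. Statistical Analysis also sets a rule for clinical events: "The primary outcome will be coded as a “failure” in the event of CHF hospitalization or mortality".

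**The concern.** Quality of life is the trial's main question, and the KCCQ is its instrument. Coding each subject as a responder or not treats a gain of 4 points like a loss of 20, and a gain of 5 like a gain of 30. Other scales in the trial, such as those for anxiety, depression and stress, suit the planned LMM and would give mean differences. The central scale would not.

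Two things are at stake. First, the secondary quality-of-life analysis uses the same coarse coding as the primary, so a real but moderate shift in the score could go undetected. Second, if the responder comparison is not significant, the reader has no estimate or interval on the KCCQ scale from which to judge what size of benefit remains plausible.

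A smaller matter concerns the top of the scale. The inclusion and exclusion criteria set no upper limit on baseline KCCQ, and a subject who starts above 95 cannot gain 5 points.

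**Working it through.** **Inputs.** From Sample Size Estimation: responder rates of 53% and 33%, alpha .05, power .80, 93 per group to replicate that effect, 21% attrition, final sample 278. Two-sided testing is assumed for the sample size; the article states it for the post hoc tests.

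**1. The plan's own figure.** Two proportions with unpooled variance:

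- n = (1.960 + 0.842)² × [0.53 × 0.47 + 0.33 × 0.67] / 0.20²
- = 7.849 × 0.4702 / 0.04 = 92.3, rounded up to 93 per group.

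This matches the article. The pooled-variance formula gives 96. The responder planning for 53% vs 33% is therefore sound.

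**2. Information kept by the cut.** If change scores are normal with equal SD in both arms, the share of information retained when a fraction p exceeds the cut is φ(z_p)² / [p(1 − p)]:

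| Responder rate p | φ(z_p)² | p(1 − p) | Retained | Lost |
|---|---|---|---|---|
| 33% | 0.1312 | 0.2211 | 0.593 | 41% |
| 43% (mean of the two) | 0.1543 | 0.2451 | 0.629 | 37% |
| 53% | 0.1583 | 0.2491 | 0.635 | 36% |

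**3. Shift implied by the planning rates.** Under the same model:

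- d = z(0.53) − z(0.33) = 0.075 + 0.440 = 0.515 SD.
- Continuous n = 2 × (1.960 + 0.842)² / 0.515² = 59.1, so about 60 per group, against 93 (article) or 96 (pooled) for the responder comparison.

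**4. Power at the expected number of completers.** 278 × 0.79 / 2 = 109.8, taken as 110 per group.

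- Responder: SE = √(0.4702 / 110) = 0.0654. Power = Φ(0.20 / 0.0654 − 1.960) = Φ(1.099) = 0.864. The pooled test gives 0.855.
- Continuous: power = Φ(0.515 × √(110 / 2) − 1.960) = Φ(1.861) = 0.969.

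**5. Ceiling.** The maximum is 100, so a gain of 5 requires a baseline of 95 or lower. A subject above 95 is a non-responder in either arm. Baseline KCCQ as a covariate does not change that. The article gives no baseline KCCQ distribution, so the share affected cannot be worked out.

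**The case against.** **The responder endpoint is coherent.** Its threshold is one the article calls clinically meaningful and supports with a citation. The trial is sized on responder rates, and a binary outcome accommodates the rule that CHF hospitalization or death counts as failure. At 110 per group its power for 53% vs 33% exceeds the 80% target. This stands. A reader might infer that the primary endpoint is wrong or the trial underpowered because of the dichotomy; the figures do not show that. With the primary unchanged, the gain in precision goes only to the secondary quality-of-life analysis.

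**A journal article may leave supportive analyses to the full plan.** That would answer a mere silence. Here the text places the KCCQ among the binary outcomes and keeps the LMM for continuous ones, so this is a stated choice. A fuller plan could still add a score analysis.

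**The normal model omits clinical events.** The Introduction cites a 1-year hospital readmission rate of 40%, so failures by rule may not be rare. A score analysis cannot inherit the failure coding and answers a somewhat different question. This stands and shapes the fix.

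**The ceiling.** It is tempting to shrink both rates by an assumed share of subjects above 95 and quote lost power. The documents do not support this. The share is unknown, and the 53% and 33% were observed on the same criterion, so they may already include such subjects. Nor would the LMM remove the ceiling: someone starting at 97 can gain at most 3 points in any analysis.

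**Planning Phase 3.** A reader might argue that a mean KCCQ difference is needed to plan the later trial. The Discussion describes that trial in terms of heart-failure hospitalizations and mortality, so the argument fails.

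**Conclusion.** The point holds as a limitation of the secondary quality-of-life analysis, not as an error in the primary endpoint or in its sample size. As described, the KCCQ score is never analysed as a score at either visit.

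Under normal, equal-SD change scores, dichotomising loses about 36-41% of the information. At the planning effect of 0.515 SD and 110 per group, that is about 86% power for the responder comparison and 97% for the score. These figures rest on that assumption, on the planning rates applying here, and on leaving the failure rule out of the continuous comparison. They indicate the size of the loss and do not predict the power of the model as it will be fitted.

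That a baseline above 95 can never meet the criterion is certain from the scale. How much it matters cannot be judged from the article.

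**What to change.** 1. Keep the responder outcome as primary.
2. For the secondary quality-of-life hypothesis, analyse the KCCQ summary score as a continuous outcome at 4 and 12 months. Use the LMM already specified (baseline KCCQ, age, sex, body mass index, time, Group) and add Group by time, so that the 12-month effect is estimated directly. Report the 12-month adjusted mean difference with its 95% CI beside the responder result.
3. State in advance how deaths and CHF hospitalizations enter that analysis, for example a while-alive estimand with a sensitivity analysis.
4. Report the number of subjects per arm with a baseline KCCQ above 95.

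The cost is one model on data already being collected and one count per arm, with no change to the visits, the sample size or the primary endpoint. The downside is one extra secondary estimate whose estimand differs somewhat from that of the responder endpoint, which the report should say.

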#### Secondary Outcomes

The quality of life at the 4-month interval will be assessed by determining the number of subjects who demonstrate a ≥5-point improvement of the KCCQ total score [38,39].

The subjects’ increase in adherence to the recommended intake of vegetables, fruit, dairy, and dietary fat will be evaluated at the 4- and 12-month assessments using the Canadian version [40] of the DHQ II [75], which is also available in French.

The physical activity level of the subjects will be measured in two ways: (1) mean step count, and (2) self-report questionnaire. We will ask subjects to document their daily step count for 7 days prior to their assessments at baseline, 4-, and 12 months. The step count will be measured using an accelerometer (LifeSource/A&D XL-18CN Activity Monitor) that we will provide to each subject. We will calculate the mean 4-day step count using data from the three weekdays and one weekend day that have the highest step count out of the 7-day record [76,77]. Adherence to physical activity over the past week will be measured by the PASE [78], which has been validated in persons with CHF [79]. We will use a French version that was translated by its publisher.

We will confirm the smoking status of those who self-report as a current smoker at the baseline, 4-, and 12-month assessments using salivary cotinine. The current smokers will be defined by having salivary cotinine level ≥10 ng/ml. These subjects will also be screened for the use of nicotine replacement therapy, which can confound their salivary cotinine result. Smoking history will be evaluated using questions from the Survey on Living with Chronic Disease in Canada [80] (ie, “Have you smoked at least 100 cigarettes in your life?”). The French version [80] of the smoking history questions will be also used in this trial.

We will estimate each subject’s medication adherence using MPR [81]. It calculates the cumulative medication supply for *x* days, divided by the total days to the next reﬁll or end of the observation period. MPR has been validated in a previous trial [20]. We will measure MPR with pharmacy refill data for a 4-month period that precedes each of the three assessments.

Anxiety will be measured using the GAD-7 scale [44]. Depressive symptoms will be assessed using the total score from the PHQ-9 [45]. Both questionnaires have been used extensively in health research and have been well validated, including in people with CHF [44,82]. French versions of the GAD-7 and PHQ-9, freely available on the Internet, will also be employed. These assessments will be made at the baseline, 4-, and 12-month intervals.

The 10-item PSS [46] is a commonly used instrument to measure the extent to which one’s life is appraised as stressful. It has demonstrated adequate reliability (Cronbach alpha=.78). The PSS has been used in people with heart disease, including CHF [83]. We will use a validated French version of the PSS for this trial [84] at the baseline, 4-, and 12-month assessments.

Readiness for change in self-care will be assessed using Prochaska’s transtheoretical algorithm [47] at the baseline, 4-, and 12-month intervals. This algorithm categorizes “readiness” to make behavioral changes in one of five stages: (1) precontemplation (do not intend to make a behavioral change in the next six months), (2) contemplation (intend to start making behavioral changes within the next six months), (3) preparation (ready to start making behavioral changes within the next 30 days), (4) action (have made changes to a behavior within the last six months), and (5) maintenance (continue with the new behavior that was changed six or more months ago).

The functional capacity of the subjects will be assessed using the 6MWT [85] at the baseline and 12-month intervals. In accordance with the American Thoracic Society’s protocol, the test will use an indoor straight course of 30-40 meters and standard instructions to “walk as far as possible in six minutes.” Values will be expressed as the percent predicted value, rather than absolute distance, because the former is less susceptible to confounding factors [86].

Autonomic nervous system function of the subjects will be assessed using heart rate variability. A 10-minute recording will be collected using a three-lead ECG. The data will be sampled at 1000 Hz using LabView (version 7.1, National Instruments). A custom heart rate variability software will be used to analyze RR interval data using a fast Fourier transformation to obtain low frequency (0.04-0.15 Hz) and high frequency (0.15-0.50 Hz) spectral components. Only the Toronto sample will be asked to provide an ECG recording at baseline and 12-month intervals.

Peak aerobic power (VO_2_ peak, oxygen consumption) and the VE/VCO_2_ (rate of elimination of carbon dioxide) slope will be used to assess exercise capacity of the subjects at the baseline and 12-month intervals. The VO_2_ peak has prognostic value [87]. It is associated with the quality of life [88], and it is sensitive to change following home-based training with telehealth in CHF patients [55]. We will be collecting this information on the subjects through medical chart review.

The SHFM provides a risk estimate that has been validated among patients with CHF [49-51]. It is derived from prognostic variables (diuretic dose/kg, systolic blood pressure, percent lymphocytes, haemoglobin, etiology, ejection fraction, cholesterol, uric acid, allopurinol, serum sodium, statin, NYHA class, age, and sex) that are easily obtained from medical charts. We will review the medical charts of the subjects to extract values for these abovementioned variables at the baseline and 12-month intervals. These will then be inserted into a freely available algorithm on the Internet. The generated SHFM score will be used in our analyses.

The brain natriuretic peptide (BNP) is a neurohormone that is synthesized in and secreted from the ventricular myocardium in response to elevated ventricular wall tension and stretch, and from the activation of the sympathetic and renin-angiotensin systems. BNP is increased in patients with CHF [89], and it correlates with risk for all-cause, cardiac, and pump-failure mortality. Proinflammatory hsCRP is elevated in CHF as the disease progresses [52,54]. We will extract these data, if available, from the medical charts of subjects at the baseline and 12-month assessments.

We will also collect the anthropometric variables such as age, sex, height and weight (for body mass index), waist circumference, medications, alcohol (drinks/day), and medical history for each subject at the baseline and 12-month assessments.

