**Methods:**

Canadian e-Platform to Promote Behavioral Self-Management in Chronic Heart Failure (CHF-CePPORT) is a multi-site, double blind, randomized controlled trial with a 2 parallel-group (e-Counseling + Usual Care vs e-Info Control + Usual Care) by 3 assessments (baseline, 4-, and 12-month) design. We will identify subjects with New York Heart Association Class II or III systolic heart failure from collaborating CHF clinics and then recruit them (n=278) by phone. Subjects will be randomized in blocks within each site (Toronto, Montreal, and Vancouver). The primary outcome will be improved quality of life, defined as an increased number of subjects with an improvement of ≥5 points on the summary score of the Kansas City Cardiomyopathy Questionnaire. We will also assess the following secondary outcomes: (1) diet habits, depression, anxiety, smoking history, stress level, and readiness for change using self-report questionnaires, (2) physical activity level, current smoking status, and vagal-heart rate modulation by physiological tests, and (3) exercise capacity, prognostic indicators of cardiovascular functioning, and medication adherence through medical chart review. The primary outcome will be analyzed using generalized estimation equations with repeated measures on an intention-to-treat basis. Secondary outcomes will be analyzed using repeated-measures linear mixed models with a random effects intercept. All significant main effects or interactions in the statistical models will be followed up with post hoc contrasts using a Bonferroni correction with a 2-sided statistical significance criterion of *P*<.05.

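### As plainly read, cotinine is taken only from self-reported smokers, so false quit reports go untested; the smoking model also adjusts for baseline KCCQ, not baseline smoking

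*Protocol article*

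**What the plan says.** **Measurement.** Under Secondary Outcomes, the protocol article states: "We will confirm the smoking status of those who self-report as a current smoker at the baseline, 4-, and 12-month assessments using salivary cotinine". It then sets the classification rule, "The current smokers will be defined by having salivary cotinine level ≥10 ng/ml", and adds a check on the same people: "These subjects will also be screened for the use of nicotine replacement therapy, which can confound their salivary cotinine result". The Methods part of the abstract groups the outcome with the objectively measured ones: "physical activity level, current smoking status, and vagal-heart rate modulation by physiological tests". No cotinine sample is described for anyone who reports not smoking.

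**Analysis.** The Statistical Analysis section names smoking status as an example of a binary secondary outcome, to be analysed by a repeated-measures generalized mixed model over the 4- and 12-month visits. For that model, "Predictors will include baseline KCCQ, age, sex, body mass index, time" and Group. For continuous secondary outcomes the same paragraph instead says "Predictors will include the baseline dependent variable, age, sex, body mass index, time (4- vs 12-month assessment interval), and Group".

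**The concern.** Biochemical verification of smoking exists mainly to catch the person who still smokes but says otherwise. Testing only those who admit to smoking cannot do that. It leaves every negative status as self-report, although the plan defines the outcome by a cotinine threshold and the abstract presents it as physiologically measured.

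On the analysis side, smoking at baseline is likely to be by far the strongest predictor of smoking at follow-up. The covariate list written for the KCCQ responder outcome appears to have been applied to all binary outcomes, so smoking is adjusted for a quality-of-life score. At stake are the credibility and the precision of one declared secondary outcome.

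**Working it through.** The document gives no smoking prevalence, quit rate or power for this outcome, so there is no stated figure to reproduce. The prevalence, quit, denial and uptake rates below are assumptions. The sample size (278, or 139 per arm if allocated 1:1) and the 21% attrition come from Sample Size Estimation.

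**Step 1: what the test can change.**

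| Report at visit | Tested (plain reading) | Possible reclassification |
|---|---|---|
| Current smoker | Yes | Smoker to non-smoker, if cotinine is below 10 ng/ml |
| Not smoking, including a baseline smoker who reports quitting | No | None |

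An untested subject has no cotinine value, so the threshold definition cannot be applied to them.

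**Step 2: effect of false quit reports.** Let q be the true quit rate among baseline smokers and f the share of continuing smokers who deny smoking. The observed quit rate is q + (1 − q)f.

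- *Unequal denial, no true effect* (q = 10% in both arms). With f = 10% in control, the observed rate is 0.10 + 0.90 × 0.10 = 19%. With f = 20% in e-Counseling it is 0.10 + 0.90 × 0.20 = 28%, a spurious 9 points. With f = 30% it is 37%, a spurious 18 points.
- *Equal denial, true effect* (q = 10% vs 20%):

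| f in both arms | Observed quit rates | Difference | Odds ratio |
|---|---|---|---|
| 0% | 10% vs 20% | 10 points | 2.25 |
| 10% | 19% vs 28% | 9 points | 1.66 |
| 20% | 28% vs 36% | 8 points | 1.45 |
| 30% | 37% vs 44% | 7 points | 1.34 |

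These are points among baseline smokers. The planned outcome is smoking status in all subjects. At 15% baseline smoking, a spurious 9 points among smokers becomes 0.15 × 9 = 1.35 points of overall prevalence.

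**Step 3: cost of leaving out baseline smoking.** At 15% prevalence there are 139 × 0.15 ≈ 21 baseline smokers per arm (14 to 28 at 10% to 20%). The standard deviation of the chance difference in baseline smoking between arms is √(2 × 0.15 × 0.85 / 139) = 4.3 points. Ten points more quitting among smokers moves overall prevalence by 0.15 × 10 = 1.5 points. Without baseline smoking in the model, that between-subject variation stays in the error.

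Power was simulated with a 12-month logistic model, 15% baseline smokers and 2% smoking at follow-up among baseline non-smokers. An uninformative covariate stood in for baseline KCCQ. The lower sample size is 278 × 0.79 ≈ 220, or 110 per arm.

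| Quit rates, control vs e-Counseling | Per arm | Power without baseline smoking | Power with it |
|---|---|---|---|
| 15% vs 40% | 139 | about 14% | about 26% |
| 15% vs 50% | 139 | about 28% | about 48% |
| 15% vs 40% | 110 | about 12% | about 20% |
| 15% vs 50% | 110 | about 20% | about 39% |

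With quit rates of 10% vs 40% at 139 per arm, power is about 11%, 18% and 26% without baseline smoking and 19%, 37% and 55% with it, at baseline prevalences of 10%, 15% and 20%. The simulation uses one follow-up visit rather than the planned two-visit model, so it shows the relative loss, not the exact power.

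**The case against.** **The sentence has another reading.** It could mean that people identified as smokers give samples at all three visits, which would catch a baseline smoker who later claims to have quit. The cotinine definition and the abstract fit that intention. This stands as a possibility, so it cannot be said that false quitting would never be detected. But nothing in the section says that baseline smokers are retested whatever they report, and a site following the plain wording would not collect those samples. Even on the other reading, a smoker who denies smoking at baseline is untested.

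**A reader might infer that false quit reports will be more common with e-Counseling and so be counted as benefit.** The document does not support that. Under Control Group, the comparison arm also receives smoke-free-living advice on the same schedule, and Randomization and Blinding states that subjects will not know their assignment. Stage-tailored messages and readiness procedures go only to e-Counseling, so a difference is possible, but its direction and size are unknown.

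**A reader might infer that omitting baseline smoking biases the result or swamps any effect.** It does neither. Randomization keeps the comparison unbiased in expectation, and chance imbalance is reflected in the standard error. The loss is precision, and power is low even with the right covariate.

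**The covariate list may be condensed and is not expressly exclusive.** That is fair, and an unseen analysis plan may add terms. But the article does fix a list, applies it by name to smoking status, and in the same paragraph uses the outcome's own baseline for continuous measures. The text as written therefore does not suit this outcome.

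**Conclusion.** Both points hold in limited form. As plainly worded, the cotinine procedure can remove people from the smoker class but cannot detect a baseline smoker who wrongly reports quitting, which sits badly with the plan's own definition of the outcome. Equal misreporting would shrink a true effect: at 20% denial, from 10 to 8 points among baseline smokers. Unequal misreporting could produce a false one: 9 points with 10% vs 20% denial. All denial and quit rates here are assumed.

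The smoking model's covariate list is the wrong one for that outcome. On the assumed inputs, leaving out baseline smoking roughly halves power (about 14% vs 26% in the main case), without bias in expectation. With about 21 baseline smokers per arm at 15% prevalence, the outcome remains underpowered after correction.

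The reach is one secondary outcome, which is not among the numbered secondary hypotheses. The primary outcome, its model and the sample size are untouched. The changes are worth making because they are cheap and because samples not taken at a visit cannot be recovered.

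**What to change.** 1. **Statistical Analysis.** In the binary secondary models, replace baseline KCCQ with the baseline value of the outcome being analysed: baseline smoking status for smoking, and baseline KCCQ kept for the KCCQ outcome. Alternatively, define the smoking analysis as abstinence among baseline smokers. The data are already collected at baseline, so this costs only a wording change.
2. **Secondary Outcomes.** State that cotinine is collected at 4 and 12 months from every baseline smoker whatever they then report, with the same screen for nicotine replacement. Count a cotinine-positive reported quitter who is not using nicotine replacement as smoking, and say how those who are using it will be classified.

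The second change needs only a small number of extra runs of an assay already in the protocol, at in-person visits already scheduled under Data Collection. It would still miss smokers who deny smoking at baseline. Testing every subject would cover them, at higher cost.
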